#### HF registry

The HF registry is an ongoing quality registry in the Netherlands facilitated by the NHR, a non-profit organisation that aims to contribute to quality improvement and safety in cardiac care.^29 30^ The HF registry serves as an ongoing learning healthcare system through benchmarking and quality control. Since 2019, it has been introduced as a voluntary, nationwide HF registration. Patient data are collected non-consecutively, and for the registry no informed consent is asked. Data of included patients are collected at three timepoints: at baseline, 6 months and 12 months from the time since diagnosis. The HF registry includes variables on three levels defined in a data dictionary: patient characteristics, treatment characteristics and clinically relevant outcomes. The data dictionary is a dynamic document (ie, the included variables and definitions may change over time) because it is based on current HF guidelines and compiled by a committee consisting of delegated cardiologists from Dutch hospitals. A detailed up-to-date data dictionary with an overview of the variables collected within the HF registry is always published on the NHR website. Online supplemental material 1 provides an overview of the data dictionary of the HF registry, September 2022 version; the content is subject to change.^31^

10.1136/bmjopen-2023-078021.supp1Supplementary data

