### Outcome measures

#### Primary outcome

The number of days alive without unplanned hospitalisation within 1 year of follow-up is derived from the number of unplanned hospital days as collected in the HF registry (table 1).

**Table 1 T1:** Operationalisation of exposure variable and study outcomes

Variable	Source	Time of collection	Operationalisation
Exposure			
Telemedicine	HF registry, telemedicine-generated data	T0, T1*, T2	Whether a patient receives telemedicine. Five categories: (1) no telemonitoring†; (2) telemonitoring by telephone; (3) telemonitoring, non-invasive based on traditional parameters (eg, blood pressure, ECG); (4) telemonitoring using ICD based on HF parameters; and (5) telemonitoring, invasive using sensors in the bloodstream or heart.
Primary outcome			
Number of days spent alive without unplanned hospitalisations within 1 year of follow-up	HF registry	T1*, T2	Number of days directly related to unplanned cardiac hospital admission due to HF. Number of admission days will be summed up over a period between follow-up moments and subtracted from 365 days.
Secondary outcomes			
Costs	Derived from HF registry, external data source, EHR, interviews	T0, T1*, T2	Costs estimated from patient, disease and treatment characteristics. Information taken into account includes medication use, whether the patient underwent cardiac interventions (eg, pacemaker implantation, percutaneous coronary intervention), use of telemedicine, hospital admission days, visits to the outpatient clinic, visits to the emergency room, admission days at an intensive care unit and visits to the GP related to HF.
All-cause mortality	HF registry, external data source	T1*, T2	Mortality status, determined after verification at the Personal Records Database (in Dutch: Basisregistratie Personen). Mortality is independent of HF (all-cause).
Functional status	HF registry	T0, T1*, T2	NYHA classification: a functional classification of patients based on severity of symptoms and physical activity, with specific attention to fatigue, palpitation and dyspnoea. Scores are linked to one of four NYHA classes: class I: no limitation; class II: slight limitation; class III: marked limitation; and class IV: unable to carry on any physical activity without discomfort.^1^

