### Exposure measurement

Exposure to telemedicine is measured in the HF registry at 6 months and 12 months of follow-up as non-use of telemedicine, telephone only, non-invasive telemedicine, implantable cardioverter defibrillator-based telemedicine or invasive telemedicine (table 1). Telemedicine output can be different from the closed-ended interviews that correspond to all outpatient clinic contacts in general. The components of the telemedicine intervention will be assessed at the hospital level at one time during the follow-up period. Table 2 provides an overview and operationalisation of the main components of the telemedicine intervention that have been described in existing literature or at the local (eg, hospital) level.^7 32–34^ The components will be validated and possibly further refined based on the interviews. Figure 3 illustrates the flow of data collected at the hospital level and at the patient level.

**Table 2 T2:** Overview and operationalisation of telemedicine variables collected in the qualitative study

Component	Definition	Operationalisation (examples)
Supplier	(External) supplier of telemedicine for patients with HF.	Sanacoach, Luscii, Motiva/Philips, linked in personal environment in EHR.
Purpose of telemedicine	The intention/motives for which the telemedicine intervention is administered: patient level and/or hospital level.	Monitoring, prevent exacerbation, reduce workload, reduce costs, patient-centred care.
Considering telemedicine	First time a clinician considered telemedicine in HF management.	After diagnosis, (re)hospitalisation, titration phase.
Structured telephone support	Structured monitoring by telephone without using applications or devices specific to telemedicine and monitoring HF.	Present or not present.
Applications	Technologies or platforms on which the patient could receive telemedicine.	Smartphone, tablet, laptop, television, smartwatch.
Devices	Accessory a patient could use to perform telemedicine.	Blood pressure device (with or without Bluetooth), weight scale (with or without Bluetooth), smartwatch.
Involved healthcare workers	Involved healthcare workers and their role in considering and executing telemedicine.	HF nurse, nurse specialist, cardiologist.
Control centrum	The presence or absence of a control centrum to check the submitted measurements and questions.	Present or not present.

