### Data collection and quality control

Data of the HF registry will be remotely monitored for major outliers and missing variables using the NHR; these processes have been described elsewhere.^30 35^ The NHR uses a unique individual patient identifier (NHRpersonID) to deduplicate registrations of the same patient (at the same or different hospitals) in the HF registry.^36^ During the RELEASE-HF study, researchers will perform an additional check on completed data and provide assistance to hospitals to reduce missing values, as well as assistance to reduce registration burden.

Telemedicine interviews, using an interview guide with closed-ended questions, will be performed by a RELEASE-HF investigator and conducted with clinicians (eg, cardiologist, HF nurse, nurse specialist, physician assistant). Interviews will be held during the 36-month period of data collection. All hospitals with telemedicine in HF care will be interviewed once, and the data will be checked with the hospitals once during the data collection period to be aware of changes in the components and status of telemedicine. For each hospital, the 6-monthly costs of telemedicine are determined via interviews and registration data (if at hand). The units will be linked to the unit cost guideline provided by the Dutch National Health Care Institute (Dutch: Zorginstituut Nederland).^37^ These interviews will be performed by a health technology assessment (HTA) scientist and conducted with clinicians or finance department staff. All participants will provide informed consent.

Patient-level telemedicine data are collected by a clinician, data manager or researcher at the hospital where the patient is being treated because these individuals have access to the identification log of the HF registry. Collected data will include the start date of telemedicine use and the frequency at which measurements are sent to the treating hospital, with a high rate typically referred to as a high-intensity (or acute) protocol and a low rate as a low-intensity (or stable) protocol.

The Heart4Data consortium will establish opportunities for data linkage between the HF registry and other national registry databases, in collaboration with public partners (figure 2).^28^ At the time of writing, a collaboration between these databases and the HF registry is not yet established for all external national databases.

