##### Preparation of the statistical model

As a first step, we describe how the overall effect of offering any type of telemedicine versus not offering telemedicine will be estimated. This analysis will subsequently be used for a comparison of telemedicine effects on days alive without unplanned HF-related hospitalisation during 1 year across subgroups.

The cohort is restricted to individuals with newly diagnosed HF, that is, at most 3 months prior to baseline. The exposure contrast is defined as offering any type of telemedicine after first presentation with HF at the hospital outpatient clinic versus patients not offered telemedicine. The telemedicine status for the entire follow-up is defined by 6 months after baseline measurement of telemedicine, used as an observational analogue of an ‘intention to treat’ analysis in which the stopping of telemedicine is disregarded.

Because telemedicine administration is dependent on patient characteristics, confounding by indication will be accounted for. Based on clinical consensus, the following patient-level confounding variables measured at baseline will be adjusted for: age, sex, SES, BMI, NYHA, LVEF, aetiology of HF, systolic blood pressure, diastolic blood pressure, heart rhythm, heart rate, chronic respiratory disorders, OSAS, stroke, extra cardiac arterial vascular pathology, DM, hypertension, anaemia, CKD, malignancy, heart rhythm disorders, depression and thyroid disease (see table 3 and online supplemental material 1).

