The primary outcome model is a linear mixed model with a random intercept for the participating centre and is specified as follows. The outcome is measured in days, and because the final measurement may be less or more than 365 days after baseline, we rescale the number of days of unplanned hospitalisation to the number of days under follow-up to 365 days. The outcome is computed by subtracting the days of unplanned hospitalisation or death from 365. The earlier described confounding variables are added to the primary outcome model to adjust for confounding. Continuous covariates are modelled using splines. Multicollinearity between confounding variables and the telemedicine status is evaluated. The coefficient for telemedicine in the primary outcome model represents the average treatment effect of offering any telemedicine within 3 months after HF diagnosis compared with not offering telemedicine on days with unplanned HF-related hospitalisation during a year in the population of patients with newly diagnosed HF. Robust SEs are estimated to compute CIs.

For the secondary outcome functional status, a similar approach is taken to estimate the average treatment effect of offering any telemedicine within 3 months after HF diagnosis compared with not offering telemedicine on functional status after 1 year in the population of patients with newly diagnosed HF. For this analysis, the outcome model is a multinomial regression model, and baseline functional status is added as a covariate. The risk difference relative to the reference outcome category is assessed using the predicted outcomes of the primary outcome model offering of telemedicine versus not offering, to obtain the marginal risk difference.^38–40^ Similarly, for the secondary outcomes health status and hrQoL, the outcome model is a probit regression model, with baseline measurements added as a covariate. Healthcare utilisation will be assessed using a Poisson regression model, and all-cause mortality will be assessed using binary logistic regression.

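### The telemedicine coefficient is described as the effect of an offer within 3 months of diagnosis, but exposure is coded from the 6-month reading with no such limit

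*Protocol article*

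**What the plan says.** All references are to the protocol article.

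- **Meaning given to the coefficient** (Preparation of the statistical model): it "represents the average treatment effect of offering any telemedicine within 3 months after HF diagnosis compared with not offering telemedicine". The same 3-month wording is used again for functional status.
- **Contrast as first defined** (same section): "The exposure contrast is defined as offering any type of telemedicine after first presentation with HF at the hospital outpatient clinic". No time limit is attached.
- **Coding rule** (same section): "The telemedicine status for the entire follow-up is defined by 6 months after baseline measurement of telemedicine". Research question 2 likewise takes the offer of telemedicine from the measurement 6 months after baseline.
- **Cohort entry** (same section): "The cohort is restricted to individuals with newly diagnosed HF, that is, at most 3 months prior to baseline". Here the 3 months run from diagnosis to baseline and say nothing about when telemedicine began.
- **Measurement times** (Exposure measurement): "Exposure to telemedicine is measured in the HF registry at 6 months and 12 months of follow-up". Table 1 also lists T0. The registry item in Table 1 is "Whether a patient receives telemedicine".
- **Registry clock** (HF registry): data are collected "at baseline, 6 months and 12 months from the time since diagnosis".
- **Start dates** (Data collection and quality control): "Collected data will include the start date of telemedicine use and the frequency at which measurements are sent to the treating hospital". The primary coding rule does not use this date.
- **Subgroups** (Research question 1): the stratified analyses estimate the effect as already defined, so they take over the same description.

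**The concern.** The rule that builds the exposure variable and the sentence that interprets its coefficient describe two different exposures. One is an offer made within 3 months of diagnosis. The other is telemedicine in use at the T1 reading, whenever it began.

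Later starts are foreseeable. Table 2 gives a (re)hospitalisation and the titration phase, besides the time after diagnosis, as occasions on which telemedicine is first considered. Patients who start on those occasions and are still on telemedicine at T1 enter the exposed group.

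What is at stake is what the primary estimate can be said to show. As worded, the report would attribute the result to early offering, a timing claim that the coded variable does not test. The same attribution would pass to functional status and to each subgroup in research question 1.

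**Working it through.** The plan gives no figure for start times, so there is nothing of its own to reproduce. No sample-size figure enters this point or changes because of it.

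**Step 1. When T1 falls after diagnosis.** Let L be the time in months from diagnosis to baseline.
- Cohort-entry rule: L lies between 0 and 3, so T1 = L + 6, which is 6 to 9 months after diagnosis.
- Registry clock run from diagnosis: T1 = 6 months.

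**Step 2. Which starts are coded exposed but lie outside the declared window.** These are starts after month 3 and up to T1, a span of T1 − 3 months.
- T1 at month 6: 6 − 3 = 3 months.
- T1 at month 9: 9 − 3 = 6 months. With L = 3, every start after baseline is outside the declared window.

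An example: baseline at month 2.5, start at month 8, T1 at month 8.5. This patient is coded exposed and described as offered telemedicine within 3 months of diagnosis. On the registry clock (T1 at month 6), a start at month 5 gives the same result. The mismatch is therefore present on either clock.

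**Step 3. How many such patients there could be.** The documents give no distribution of start times. The figures below are assumptions that show a range, with everyone who starts before T1 taken to be still on telemedicine at T1.

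*Starts uniform from diagnosis to T1:* late share = (T1 − 3)/T1.
- T1 = 6: 3/6 = 50%.
- T1 = 9: 6/9 = 67%.
- L uniform on 0 to 3: the mean in-window share is (1/3)∫₀³ 3/(6+L) dL = ln(9/6) = 0.41, so 59% are late.

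*Starts front-loaded (exponential from diagnosis with mean m months, truncated at T1):* late share = 1 − (1 − e^(−3/m))/(1 − e^(−T1/m)).

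| m (months) | T1 = 6 | T1 = 9 |
|---|---|---|
| 1 | 1 − 0.950/0.998 = 5% | 1 − 0.950/1.000 = 5% |
| 3 | 1 − 0.632/0.865 = 27% | 1 − 0.632/0.950 = 33% |

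**Step 4. What mixing could do to the coefficient.** For illustration only, take the 6.4 days from the sample size section as the early-offer effect and assume that late starters obtain half of it. The coefficient is then 6.4 × (1 − s/2) for a late share s:
- s = 5%: 6.2 days
- s = 27%: 5.5 days
- s = 50%: 4.8 days
- s = 67%: 4.3 days

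This leaves out the fact that a patient must survive to start late, which could push the estimate the other way. The direction of any net error is therefore not established.

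**Step 5. Whether the planned additional analyses resolve it.** Restarting follow-up at T1 changes when outcome days are counted, not when telemedicine began. The misclassification it is meant to address is telemedicine started soon after baseline but not registered. The per-protocol analysis depends on linkage. Neither aligns the description of the primary coefficient with its coding.

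**The case against.** The strongest reply is that this is a slip of wording. Every other statement of the contrast lacks the window, the operative rule is clear, and no model term or sample-size figure depends on the phrase. That it is probably a slip stands. But the phrase sits in the sentence that says what the primary estimate means, it is repeated for functional status, and the subgroup analyses rely on it. It cannot be read as describing the population either, because the same sentence names the newly diagnosed population separately.

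Three stronger readings are tempting, and the documents do not support them.

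- **That most of the exposed group started late.** A calculation that lets starts begin only at baseline gives a larger late share, but it leaves out starts between diagnosis and baseline, all of which are inside the window. Table 1 lists exposure at T0 and Table 2 lists the time after diagnosis as an occasion for considering telemedicine, so such starts are foreseen. The true share cannot be derived.
- **That the study will issue a recommendation on timing.** The Introduction calls for clarity on when telemedicine should be given, but none of the four objectives concerns timing, and no recommendation for a 3-month offer is announced.
- **That later starters should be recoded as unexposed.** This would put telemedicine recipients into a comparator that the plan defines as patients not offered it, and so replace a mislabelled exposed group with a contaminated control group.

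It is also fair that start dates may be incomplete. The article's list of limitations says that most telemedicine data are at hospital level, and the per-protocol analysis treats detailed information on starting and stopping as conditional on linkage.

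**Conclusion.** The point holds as an inconsistency between the stated effect and the coded exposure. It rests on the article's own text and needs no assumption: on either clock, starts from month 3 up to T1 count as exposed although they lie outside the declared window. The 3-month limit appears to have been carried over from the cohort-entry criterion.

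The size is unknown. Under the assumed start patterns the late share runs from about 5% (strongly front-loaded) to 50–67% (uniform from diagnosis to T1). These figures illustrate a range and do not estimate it. The finding is that the coefficient is misdescribed. It is not shown that the estimate is biased in a known direction or by a known amount. The correction should be made because it determines what the primary result may be said to show.

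**What to change.** Under Preparation of the statistical model, delete the 3-month-after-diagnosis qualifier in both places (primary outcome and functional status). Restate the coefficient as the effect of telemedicine status at the 6-month registry reading, with telemedicine started at any time up to T1, versus no telemedicine at that reading, in patients with newly diagnosed HF. Research question 1 then inherits the right description. This is a wording change and costs nothing. It does give up the claim about early offering, which the coding does not support.

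Optionally, where the planned patient-level start dates are available, add a sensitivity analysis with two exposed groups: starts within 3 months of diagnosis and later starts. Compare each with patients never on telemedicine, and do not move later starters into the unexposed group. The cost is dependence on how complete the start dates are, and smaller exposed groups. The later-start comparison also needs caution, because those patients had to survive to their start.

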Health status	HF registry	T0, T1*, T2	SF-36 or SF-12 questionnaire (subset of SF-36)^54^: a validated patient-reported survey of patient health. Both questionnaires consist of eight sections with scores: vitality, physical functioning, bodily pain, general health perceptions, physical role functioning, emotional role functioning, social role functioning and mental health. Each score is transformed into a scale of 0–100 on the assumption that each question carries equal weight. The lower the score, the more disability.
Health-related quality of life	HF registry	T0, T1*, T2	SF-36 or SF-12 questionnaire. QALY will be calculated based on the SF-6D, a model in which a single, preference-based score can be directly calculated for the SF-36 and SF-12.^55^ Scores range from 0.0 (worst health state) to 1.0 (best health state).
Healthcare utilisation	External data source, EHR	T1, T2	Healthcare utilisation based on (1) the number of outpatient visits, plus (2) the number of visits to the general practice related to HF.

*The HF registry collects data standard at baseline (T0), after 6 months (T1) and after 12 months (T2). The RELEASE-HF study conforms to the timeframes of the HF registry. Therefore, data will be collected at 6 months, although the outcome measurements are after 12 months.

†The HF registry defines telemedicine as telemonitoring.

EHR, electronic health record; GP, general practitioner; HF, heart failure; ICD, implantable cardioverter defibrillator; NYHA, New York Heart Association; QALY, quality-adjusted life year; RELEASE-HF, REsponsible roLl-out of E-heAlth through Systematic Evaluation – Heart Failure; SF-12, 12-item short form health survey; SF-36, 36-item short form health survey; SF-6D, six-dimensional health state short form.

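### The functional-status model names all newly diagnosed patients as its target but, as written, compares only 12-month survivors; health status and hrQoL inherit the mismatch

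*Protocol article*

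**What the plan says.** All references are to the protocol article.

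- **Target.** The section *Preparation of the statistical model* defines the functional-status effect as the average treatment effect "on functional status after 1 year in the population of patients with newly diagnosed HF".
- **Scale.** Table 1 defines functional status by NYHA class: "Scores are linked to one of four NYHA classes". Death is not among them.
- **Model.** For functional status, "the outcome model is a multinomial regression model, and baseline functional status is added as a covariate". Marginal risk differences are then taken from model predictions.
- **Health status and hrQoL.** The text carries the approach over: "for the secondary outcomes health status and hrQoL, the outcome model is a probit regression model, with baseline measurements added as a covariate". For the SF-36/SF-12 sections, Table 1 says "Each score is transformed into a scale of 0–100 on the assumption that each question carries equal weight". The SF-6D runs from 0.0 to 1.0, and its zero is labelled the worst health state, not death.
- **Death elsewhere.** For the primary outcome, "The outcome is computed by subtracting the days of unplanned hospitalisation or death from 365". Separately, "all-cause mortality will be assessed using binary logistic regression". Under *Cost-effectiveness*, QALYs use observed follow-up time, so death shortens them.

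Research questions 1 and 2 reuse the same secondary-outcome models for subgroups and for telemedicine components.

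**The concern.** A patient who dies before the 12-month measurement has no NYHA class and no questionnaire score, and the article assigns none. The stated model can then be fitted only to patients alive at 12 months, while the stated effect covers everyone newly diagnosed.

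This matters if telemedicine changes survival, and the abstract and Introduction cite meta-analyses pointing to a favourable effect on mortality. Survivors with and without telemedicine are then different selections from the cohort. If the patients kept alive have worse function than the other survivors, the survivor comparison moves against telemedicine for a reason unrelated to its effect on function. In the subgroup analyses, differing mortality effects could create or hide apparent heterogeneity, which is the study's central question.

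**Working it through.** **Plan's own figure.** There is none for these models. The sample size calculation concerns only the primary outcome and is not in question here.

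**Definitions side by side.** Target: all newly diagnosed patients. Scale: four living classes. Model: one outcome level per class. Deaths: counted in the primary outcome, the mortality model and the QALY, but given no place in the NYHA, health-status or hrQoL models. Averaging model predictions over the whole cohort does not close the gap, because it gives patients who died a predicted living NYHA class.

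**How selection acts.** Let *a* be the share who survive either way, *s* the share who survive only with telemedicine, and *q* and *r* the probabilities of NYHA III/IV in those two groups. Suppose telemedicine does not change function in the first group. Then:

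- survivors only: difference in III/IV = s(r − q)/(a + s)
- counting III/IV or dead: difference = −s(1 − r)

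**Illustration (all inputs assumed).** Per 1000 patients, take 100 deaths without and 70 with telemedicine, 180 survivors in class III/IV in both, plus 18 of the 30 extra survivors. So a = 0.90, s = 0.03, q = 0.20, r = 18/30 = 0.60.

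- Survivors only: 180/900 = 20.0% versus 198/930 = 21.3%, or +1.3 points. The formula gives 0.03 × 0.40/0.93 = 0.0129.
- III/IV or dead: (180 + 100)/1000 = 28.0% versus (198 + 70)/1000 = 26.8%, or −1.2 points.

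**Range (all inputs assumed).** Take mortality without telemedicine of 5–20%, mortality ratio 0.9–0.7, q = 30% and r = 70–90%.

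| Contrast | Smallest | Largest |
|---|---|---|
| NYHA III/IV, survivors only | 0.005 × 0.4/0.955 = +0.2 points | 0.06 × 0.6/0.86 = +4.2 points |
| NYHA III/IV or dead | −0.005 × 0.1 = −0.05 points | −0.06 × 0.3 = −1.8 points |

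With an assumed SF-6D of 0.70 in those who survive either way and 0.50 in those saved, the survivor-only hrQoL difference runs from −0.005 × 0.2/0.955 = −0.001 to −0.06 × 0.2/0.86 = −0.014.

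**Sensitivity to the no-benefit assumption.** In the first illustration, 12 fewer class III/IV patients among the 900 who survive either way (12/900 = 1.3 points) removes the apparent harm: (168 + 18)/930 = 20.0%.

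**The case against.** **The article is silent rather than wrong.** It never says survivors only, and the handling of deaths in a secondary outcome is often left to a SAP. This stands only in part. The article itself fixes the population, the scale and the model, and these three do not fit together. It is true that a multinomial model does not force the exclusion of deaths; that is why the repair is easy.

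**Mortality is reported anyway.** It has its own model overall, by subgroup and by component. This helps a reader but does not make the stated population correct.

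**The planned analysis is adjusted; the illustration is not.** The model includes baseline NYHA, age, LVEF and many other covariates. Within covariate strata the distortion vanishes if the patients saved have the same NYHA distribution as the other survivors (r = q). Only selection beyond the measured covariates remains. This stands, and it means the crude figures cannot be read as the expected bias.

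**The size may be lost in noise.** Suppose all 6480 patients were split equally (generous, since the main analysis is restricted to newly diagnosed patients). Survivors would number 3240 × 0.90 = 2916 and 3240 × 0.93 = 3013. The crude 95% half-width is 1.96 × √(0.20 × 0.80/2916 + 0.213 × 0.787/3013) = 2.1 points, wider than the 1.3-point example. This also stands.

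**A death category brings its own hazard.** Telemedicine status is defined by the 6-month measurement, which patients who die earlier do not have. Counting them as not offered telemedicine would load early deaths onto the comparison group. This stands and is built into the fix.

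**Conclusion.** The mismatch between target, scale and model holds. For functional status it is explicit. For health status and hrQoL it follows from the approach being carried over and from scales with no value for death. As written, these models estimate contrasts among 12-month survivors, selected on a consequence of the exposure if telemedicine affects survival.

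A reader might infer that the plan will make a life-saving intervention look harmful. The documents do not support that. They give no mortality rate, no mortality effect for this cohort and no NYHA distribution. The sign reversal shown needs a mortality benefit, sicker patients among those saved beyond what the covariates capture, and no functional benefit. Size and direction are therefore open.

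A reader might also infer that death should simply score 0 for hrQoL. That does not fit the text either: zero on the SF-6D is defined there as the worst health state, and the stated model is a probit with no cut-point given.

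The outcomes affected are secondary, but the models feed the subgroup and component analyses, so the point should be settled before analysis.

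**What to change.** 1. **Functional status.** Add death by 12 months as a fifth level of the multinomial NYHA model and report marginal risk differences for all five levels. The stated population can then stand.
2. **Deaths before the 6-month exposure measurement.** Apply the same explicit rule as for the primary outcome. The article shows no such rule, so write it once for both. Never count these patients as unexposed by default.
3. **Health status and hrQoL.** Restate the target as patients alive at 12 months, label every such result accordingly, and show it beside the mortality result for the same contrast, including the subgroup and component analyses. Do not prescribe a score of 0 for death in the stated probit model.

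**Cost.** No new data are needed for the fifth level, because Table 1 already has vital status verified against the population register. The NYHA model gains one outcome level, and the stated population for health status and hrQoL becomes narrower. Labelling those two results does not remove survivor selection; it only stops them being read as effects in all newly diagnosed patients.
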